### Patient and public involvement

Patient and Public Involvement and Engagement (PPIE) was incorporated throughout this project. A patient/public/parent group has been formed, with consideration given to the National Institute for Health and Care Research (NIHR) INCLUDE framework, ensuring that under-served groups were represented.^47^ Focus groups were/will be held throughout the project including during results dissemination. Participants were/will be reimbursed according to NIHR guidelines.^48^

## Strengths and limitations

This TTE will benefit from the large available sample size provided by the PICANet database, as well as its representative coverage of the FIRST-ABC step-up target population.

FIRST-ABC step-up will be emulated within the constraints of routinely collected data. As in any observational study, confounding and selection bias are major concerns. We will mitigate these risks through the TTE design and a validated and rich covariate data set, which will enable the key trial eligibility criteria to be applied, and most potential confounders to be included in the adjustment.

The inclusion of healthier children compared with FIRST-ABC step-up could dilute the effect towards the null, while failing to exclude children who initiated treatment before PICU admission could artificially shorten the follow-up period, further biasing the effect towards the null. In both cases, the bias is assumed to be non-differential. Other non-replicable exclusion criteria are contraindications to the treatments, and their unavailability in PICANet is mitigated by the treatment initiator design.

Study treatments and endpoints replication is constrained by the limits imposed by routinely collected data, but preliminary checks have proved NIV to be a valid alternative to CPAP.

Because the primary outcome cannot be assessed beyond PICU discharge, we will assume that respiratory support ends at the time of PICU discharge. This assumption may introduce differential bias as HFNC is more likely than CPAP to be continued on the ward.^49^

The use of daily rather than hourly data may limit our ability to target a population fully comparable to that in FIRST-ABC and may hinder accurate identification of the treatment received. Strategies will be implemented to minimise potential differences between treatment groups.

Additionally, DR analysis methods will be implemented, and sensitivity analyses will be performed to assess the robustness of the findings. Missing data are expected to be minimal.

This study will be reported using the Strengthening the Reporting of Observational Studies in Epidemiology guidelines.^50^

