### FIRST-ABC step-up

FIRST-ABC was a master protocol of two pragmatic randomised trials to evaluate the non-inferiority of HFNC versus CPAP for NRS in paediatric critical care.^16^ For the present study, we will focus on the step-up RCT which includes critically ill children requiring NRS for an acute illness. This was powered for the primary endpoint: a sample size of 536 children was required to achieve 90% power with a one-sided type I error rate of 2.5% to exclude the prespecified non-inferiority margin of an adjusted HR of 0.75, and anticipating 5% censoring due to death or transfer. To allow for withdrawal/refusal of deferred consent, the total sample size included 600 children.^17^ Of the 600 children randomised between August 2019 and November 2021, 573 were included in the primary analysis to measure time to liberation from respiratory support using a frequentist approach. This used a modified intention-to-treat (mITT) population, which only included participants who initiated treatment. HFNC met the non-inferiority margin criterion (HR 1.03, 95% CI 0.86 to 1.22). Similar results were seen in the per-protocol analysis (HR 1.03, 95% CI 0.86 to 1.23). Secondary outcomes included mortality at critical care unit discharge (OR 1.22, 95% CI 0.32 to 4.62) and intubation at 48 hours (OR 0.99, 95% CI 0.61 to 1.62). A summary of the components of the FIRST-ABC step-up emulation is reported in table 1.

**Table 1 T1:** Specification of the FIRST-ABC step-up emulation

Protocol component	FIRST-ABC step-up RCT	Target trial emulation
Eligibility criteria	Critically ill children requiring NRS for an acute illness were eligible if meeting the following:	Children included in PICANet between 1 August 2018 and 31 March 2022 and starting HFNC or NIV (as a surrogate for CPAP) will be eligible if meeting the following:
	*Inclusion criteria*	*Inclusion criteria*
	1) Admitted/accepted for admission to PICU/HDU.	1) Admitted to PICU.
	2) Age >36 weeks corrected gestational age and <16 years.	2) Age >36 weeks corrected gestational age and <16 years.
	3) Assessed by the treating clinician to require non-invasive respiratory support for an acute illness.	NA
	*Exclusion criteria*	*Exclusion criteria*

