### Exposures

In FIRST-ABC step-up, children randomised to HFNC were started at a flow rate based on body weight. When a child was deemed ready for weaning, the flow rate was reduced by 50%. Children randomised to CPAP were started at a pressure of 7–8 cm H_2_O. When a child was deemed ready for weaning, the pressure was reduced to 5 cm H_2_O. Both HFNC and CPAP were delivered through devices and interfaces already used as part of routine care at sites. For both groups, the fraction of inspired oxygen (FiO_2_) was titrated to maintain peripheral oxygen saturation (SpO_2_) of 92% or higher. Clinicians were permitted to switch from HFNC to CPAP (or vice versa) or escalate to other modes of NRS or invasive mechanical ventilation if prespecified treatment failure criteria were met (FiO_2_ ≥0.60, severe respiratory distress, patient discomfort).

In this study, exposure groups will include children who started HFNC or NIV, as per daily interventions in the PICANet Admission Data Collection Form.^12^ CPAP is not recorded in the PICANet daily procedures and, therefore, it cannot be identified. As NIV cannot be used to record HFNC, we will use NIV as a surrogate for CPAP, providing treatment strategies for the TTE.^18^

The assumption that NIV could approximate CPAP was tested on the FIRST-ABC step-up population linked to the relevant PICANet sample using a previously reported strategy.^19^ Of the children with a recorded activity date that matched the randomisation date, or the following date, 86% of children with recorded NIV were assigned to CPAP in FIRST-ABC step-up and 86% of children with recorded HFNC were assigned to the same treatment in FIRST-ABC step-up.

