### Sample size considerations

In the design of the FIRST-ABC step-up RCT, it was anticipated that 508 observed events would achieve 90% power with a one-sided type I error rate of 2.5% to exclude the prespecified non-inferiority margin of an HR of 0.75. To account for censoring from death or transfer and refusal or withdrawal of consent, the target sample size was set at 600 children.^5^

The design of the TTE recognises that between 2019 and 2022 there were 14 875 respiratory admissions in PICANet.^21^ From a previous PICANet sample of 2 years, it was anticipated that more than 3000 children (of which 2/3 assigned to HFNC) would meet the pre-defined eligibility criteria and start the study treatments in the first 2 days of critical care admission. The primary outcome will be tested for non-inferiority using the RCT margin (corresponding to approximately a 16-hour increase in median time to liberation), and the secondary outcomes for superiority. Among the secondary outcomes, the rate of intubation at 48 hours was considered of high importance by patient representatives. With a proportion of 15.4% from FIRST-ABC step-up results, we anticipate that, with unequal group sizes, a two-sided type I error rate of 5%, and 90% power, the study will be able to detect a 4% absolute difference in proportions.^22^

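### The protocol accepts biases towards the null without saying that, in its primary non-inferiority test at HR 0.75, that direction favours the claim

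*Protocol article*

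**What the plan says.** Sample size considerations: "The primary outcome will be tested for non-inferiority using the RCT margin". The section describes the trial's design as one in which "508 observed events would achieve 90% power with a one-sided type I error rate of 2.5" per cent "to exclude the prespecified non-inferiority margin of an HR of 0.75". An HR below 1 means slower liberation on HFNC.

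Strengths and limitations names two departures from the trial population and gives the direction of each. On the first: "The inclusion of healthier children compared with FIRST-ABC step-up could dilute the effect towards the null". The second is the failure to exclude children who started treatment before PICU admission, described as "further biasing the effect towards the null. In both cases, the bias is assumed to be non-differential". The appraisal of these two biases ends there.

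Exposures reports a linkage check in which "86% of children with recorded NIV were assigned to CPAP in FIRST-ABC step-up"; the same percentage is given for HFNC. Table 1 lists a modified intention-to-treat contrast only, whereas the trial also had a per-protocol contrast. Sensitivity analyses lists a restriction on start day, alternative estimators and a negative control outcome.

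**The concern.** Calling a bias non-differential and towards the null is reassuring in a superiority test, where dilution makes a claim harder. Here the null hypothesis is an HR at or below 0.75, and the claim is made when the lower confidence limit exceeds 0.75. If HFNC were truly at the margin, dilution would move the expected estimate from 0.75 towards 1, into the region where non-inferiority is declared. The biases that the protocol describes therefore help its primary claim.

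Two features add to this. The emulation is much larger than the trial, so its standard error shrinks while the bias does not. The benchmark comparison also cannot reveal dilution, because the trial's HR is close to 1: attenuating 1.03 by as much as 28% gives 1.03^0.72 = 1.02. At stake is whether a non-inferiority statement, overall or in the subgroups named under Objectives, carries the error rate that readers will assume.

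**Working it through.** **Reproducing the plan's figures.** Schoenfeld events for a margin of 0.75, true HR 1, 1:1 allocation, one-sided 2.5% and 90% power: 4 × (1.960 + 1.282)² / (ln 0.75)² = 508, as stated. With "anticipating 5% censoring due to death or transfer", 508 / 0.95 = 535, against the 536 in the FIRST-ABC step-up section. The figures reproduce to within rounding.

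**Inputs for the emulation.**
- Margin 0.75; more than 3,000 children, two thirds on HFNC (Sample size considerations).
- Censoring of 5%, borrowed from the trial design (assumption), giving about 3,000 × 0.95 = 2,850 events.
- One-sided 2.5%, stated for the trial and not restated for the emulation (assumption).
- Attenuation *a* of the log HR: not given in the documents. Assumed range 5% to 20%, with 28% as an upper scenario.

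**Formulae.** SE = 1 / √(2,850 × 2/3 × 1/3) = 0.0397. The expected observed log HR is (1 − a) × ln(true HR). At a true HR of 0.75,

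P(declare non-inferiority) = P(Z > 1.960 − a × 0.2877 / SE).

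For a = 10%, the shift is 0.0288 / 0.0397 = 0.724, and P(Z > 1.236) = 10.8%.

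| Attenuation | Apparent HR when truth is 0.75 | 2,850 events, 2:1 | Same, variance doubled | 508 events, 1:1 | 2,850 events, true HR 0.70 |
|---|---|---|---|---|---|
| 0% | 0.750 | 2.5% | 2.5% | 2.5% | <0.1% |
| 5% | 0.761 | 5.5% | 4.4% | 3.6% | 0.1% |
| 10% | 0.772 | 10.8% | 7.4% | 5.1% | 0.3% |
| 20% | 0.794 | 30.4% | 17.5% | 9.5% | 2.9% |
| 28% | 0.813 | 52.7% | 29.9% | 14.6% | 11.8% |

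The variance-doubled column stands for the precision lost to propensity weighting.

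**Simulation check.** Cox model, 3,000 runs, 3,000 children, 2:1, about 5% censored, true HR 0.75. False non-inferiority was 2.1% with no bias. It was 4.7%, 10.4% and 25.8% when 5%, 10% and 20% of children had no treatment effect. The last figure is below 30.4% because a 20% no-effect share gave an apparent HR of 0.790, which is an attenuation of 18% (ln 0.790 / ln 0.75 = 0.82). With 14% misclassified in each recorded group the result was 53.3%.

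**Origin of 28%.** If all of the 14% disagreement in each recorded group were misclassified exposure, the log HR would be multiplied by about 0.86 + 0.86 − 1 = 0.72.

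**Away from the margin.** Suppose the emulation observes HR 1.03. Its lower limit would be about exp(0.0296 − 1.960 × 0.0397) = 0.95. The conclusion would then tip only if the log HR had been multiplied by less than ln(0.953) / ln(0.75) = 0.17, that is, attenuated by more than 83%.

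**The case against.** The strongest reply is that no figure above measures either quoted bias. Their size is not given, and the 86% agreement concerns something else. It compares recorded support with the randomised arm, so a child randomised to CPAP who actually started HFNC counts as disagreement there but is correctly classified in a cohort grouped by treatment started. Nor can the linked trial children inform dilution from healthier or previously treated children, since they met the trial's own exclusions. This stands. A reader might infer that the true error is above 50%, or that the lower limit must clear 0.75^0.72 = 0.813. The documents support neither.

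Further points stand in part:
- Under constant proportional hazards, starting the clock late leaves the HR unchanged, so the second bias need not dilute. Healthier children may be partly a different target population. But the protocol itself describes both as bias towards the null.
- Relevant work is planned: interaction by SpO2:FiO2 quintile, adjustment for candidate covariates such as source of admission, and a description of switching. None tests whether the primary conclusion survives dilution.
- The trial's interval, 0.86 to 1.22, makes a true overall HR near 0.75 unlikely, and the protocol defines a successful emulation by comparable estimates. This limits the practical consequence for the overall result. It says less about subgroups.
- Analysis detail may sit in the statistical analysis plan. The absence of a bias analysis is therefore not the finding. The point rests on what the article does fix: the margin, and a bias appraisal that omits its consequence for the test.

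**Conclusion.** The point holds as a matter of direction. By the protocol's own account two accepted biases act towards the null, and in the primary test that direction favours the claim. Non-differentiality does not remove the problem.

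The size is a range under assumption. At a true HR of 0.75, attenuation of 5%, 10% and 20% gives about 5.5%, 11% and 30% false non-inferiority instead of 2.5%, or about 7% and 17% for the last two if weighting doubles the variance. The 28% case, about 53%, is an upper scenario only, because the 86% agreement mixes misrecording with trial non-adherence. The inflation falls quickly below the margin (0.3% and 2.9% at a true HR of 0.70 with 10% and 20% attenuation) and is negligible if the truth is about 1.03. A reader might also infer that the overall conclusion is likely to be wrong; the trial's result gives no support for that.

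**What to change.** 1. In Sample size considerations and in Strengths and limitations, state that bias towards the null favours non-inferiority in this test.
2. Under Sensitivity analyses, add a supportive bias analysis of the primary test that does not bind the decision. With L the observed lower confidence limit for the HR, report the tipping value λ* = ln(L) / ln(0.75). Non-inferiority survives any dilution factor λ above λ*. If L is 1 or more, no attenuation overturns it.
3. Report the HR and its limits with their logarithms divided by λ, over a stated range such as 0.72 to 1. Say that the lower end is a scenario and not an estimate.
4. Qualify the non-inferiority claim if plausible dilution would overturn it.

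As an illustration, the trial's own lower limit of 0.86 gives λ* = ln(0.86) / ln(0.75) = 0.52, so its conclusion would survive attenuation of up to about 48%.

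The cost is a few lines of text and code, with no new data. The downside is that the claim may have to be more qualified.

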**Methods and analysis:**

This is a protocol for a TTE that will use longitudinally collected data from the PICANet database. The study aims to emulate the FIRST-ABC step-up RCT using an observational study design in a frequentist framework. We will benchmark the results against the published trial. The study will apply a new-user design by selecting children admitted to paediatric intensive care units that started HFNC or non-invasive ventilatory support (as a surrogate for CPAP). The eligibility criteria and selected outcomes will reflect those of FIRST-ABC within the constraints of the available routinely collected data. We will use advanced quantitative doubly robust methods to minimise the impact of confounding by indication and allow for heterogeneity according to child characteristics. The analysis will be repeated using a Bayesian approach for follow-up research.

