	1) Assessed by the treating clinician to require immediate intubation and invasive ventilation due to severe hypoxia, acidosis and/or respiratory distress, upper airway obstruction, inability to manage airway secretions or recurrent apnoeas.	1) Receiving invasive mechanical ventilation at treatment assignment.
	2) Tracheostomy in place.	2) Tracheostomy in place.
	3) Received HFNC/CPAP for >2 hours in the prior 24 hours.	NA
	4) On home non-invasive ventilation prior to PICU/HDU admission.	NA
	5) Presence of untreated air-leak (pneumothorax/pneumomediastinum).	NA
	6) Midfacial/craniofacial anomalies (unrepaired cleft palate, choanal atresia) or recent craniofacial surgery.	NA
	7) Agreed ‘not for intubation’ or other limitation of critical care treatment plan in place.	NA
	8) Previously recruited to the FIRST-ABC trial.	3) Previously recruited to the FIRST-ABC trial.
	9) Clinician decision to start other form of non-invasive respiratory support (ie, not HFNC or CPAP).	NA
	NA	4) Planned admission.
Treatment strategies	Children were randomised to HFNC or CPAP. Clinicians were permitted to switch from HFNC to CPAP (or vice versa) or escalate to other modes of non-invasive respiratory support or invasive mechanical ventilation if prespecified treatment failure criteria were met.	Children will be assigned to HFNC or NIV as a surrogate for CPAP.
Assignment procedure	Subjects were randomised 1:1 to treatment using a central telephone/web-based randomisation service available 24 hours/7 days per week. The randomisation sequence was computer generated and variable block sizes were used to strengthen allocation concealment. Randomisation was stratified by site and age (<12 months vs ≥12 months).	Participants will be assigned to either strategy they start at baseline. Randomisation will be emulated by adjusting for baseline covariates using advanced statistical methods.
Follow-up period	Starts at randomisation and ends at liberation from respiratory support.	Starts at initiation of HFNC or NIV and ends at liberation from respiratory support.
Outcome	*Primary endpoint*	*Primary endpoint*
	Time to liberation from respiratory support, defined as the start of a 48-hour period during which the child is free of all forms of respiratory support.	Time to liberation from respiratory support, defined as the start of a 2-day period during which the child is free of all forms of respiratory support.
	*Secondary endpoints*	*Secondary endpoints*

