### Covariates

We will use demographic and admission information to create a cohort of children that reflects the FIRST-ABC step-up sample.

Potential covariates collected at PICU admission that will be explored using directed acyclic graphs (DAGs) include, but are not limited to: age, site, ethnic group, sex, type of admission to unit, previous PICU admission, source of admission, care area admitted from, elective admission, main reason for admission, cardiac arrest before PICU admission, cardiomyopathy or myocarditis, severe combined immune deficiency, hypoplastic left heart syndrome, leukaemia or lymphoma, liver failure, acute necrotising enterocolitis, spontaneous cerebral haemorrhage, neurodegenerative disorder, HIV, bone marrow transplant receiver, systolic blood pressure, SpO_2_, FiO_2_, arterial PaO_2_, base excess, lactate, mechanical ventilation, CPAP, pupil reaction.^20^

In addition, other daily interventions as defined by the PICANet Manual will be assessed as potential covariates from PICU admission up to the start of treatment.^18^

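### Home-NIV children and starters of other NRS modes are not excluded by contraindication; they can load the NIV arm and probably favour HFNC, by an unknown amount

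*Protocol article*

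**What the plan says.** Table 1 (section FIRST-ABC step-up) sets the RCT's exclusions beside the emulation's and marks RCT exclusions 3, 4, 5, 6, 7 and 9 as not available. Exclusion 4 reads "On home non-invasive ventilation prior to PICU/HDU admission". Exclusion 9 concerns children whose clinician chose a non-invasive mode other than HFNC or CPAP. Exclusion 7 concerns a limitation of care, and exclusion 3 concerns recent HFNC or CPAP.

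Strengths and limitations handles these gaps with two separate arguments:

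- For healthier children and for treatment begun before PICU admission: "In both cases, the bias is assumed to be non-differential".
- For the rest: "Other non-replicable exclusion criteria are contraindications to the treatments, and their unavailability in PICANet is mitigated by the treatment initiator design".

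The abstract states: "The study will apply a new-user design". Exposures says that the PICANet daily procedures do not record CPAP, that HFNC cannot be entered as NIV, and that NIV therefore stands in for CPAP. The supporting check, with 86% agreement in each arm, was made on FIRST-ABC step-up participants linked to PICANet. Outcomes requires two days without any support and treats PICU discharge as liberation.

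**The concern.** A treatment initiator design can deal with contraindications, because a child with a contraindication tends not to start the treatment and so does not enter the cohort. Home NIV is not a contraindication but prior use of one of the study treatments. Starting another mode is a different treatment choice. A care limitation does not rule out HFNC or CPAP. For home NIV and other modes, the initiator rule does the opposite of what is claimed: a child recorded on NIV qualifies as an NIV starter.

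If such children collect in the comparator and come off support slowly, the liberation HR (HFNC versus NIV) is pushed upwards. The test asks whether the HR exceeds 0.75, so an upward shift makes non-inferiority easier to declare. It would also distort the benchmarking against the RCT, which excluded these children.

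**Working it through.** **1. Which arm they enter (Exposures against Table 1)**

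- *Other-mode starters:* by definition not on HFNC, and NIV cannot hold HFNC. If recorded as starting a study treatment, they can only be in the NIV arm.
- *Home-NIV children kept on NIV:* also in the NIV arm. Some could be started on HFNC; the article gives no counts.
- *Endpoint:* while NIV continues, a home-NIV child cannot have two support-free days. The event is then PICU discharge.
- *The 86% check:* RCT participants had already passed exclusions 4 and 9, so the check cannot show how many such children enter the emulation's NIV arm.

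**2. The plan's own figures**

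Events to exclude HR 0.75 at one-sided 2.5% with 90% power and 1:1 allocation:

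(1.960 + 1.282)² / (0.25 × (ln 0.75)²) = 508, as stated in Sample size considerations.

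With 5% censoring, 508 / 0.95 = 535, against 536 stated. The design figures are sound.

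**3. Illustration of size**

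*From the article:* margin 0.75; about 3000 children, two thirds HFNC (2000 versus 1000); 5% censoring (the RCT's figure).

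*Assumed, because the article gives neither:* a share f of the NIV arm consists of these children, and their liberation hazard is r times that of the other NIV children. All are placed in NIV, with no covariate adjustment.

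*Model:* exponential times with an NIV median of 2 days. This agrees with the plan's 16-hour equivalent of the margin, since 16 / (1/0.75 − 1) = 48 hours.

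- NIV: S₀(t) = (1 − f)·exp(−λt) + f·exp(−rλt), with λ = ln 2 / 2 per day
- HFNC: S₁(t) = exp(−HR·λt)
- The observed HR is the large-sample Cox value.
- SE(log HR) = 1/√(2850 × 2/9) = 0.0397, where 2850 = 0.95 × 3000
- False non-inferiority = 1 − Φ(1.96 − ln(HR_obs/0.75)/SE)

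| f | r | HR_obs, true 0.75 | False non-inferiority | HR_obs, true 1.00 |
|---|---|---|---|---|
| 0 | – | 0.750 | 2.5% | 1.00 |
| 2% | 0.5 | 0.765 | 7% | 1.02 |
| 2% | 0.33 | 0.779 | 16% | 1.03 |
| 5% | 0.5 | 0.787 | 23% | 1.05 |
| 5% | 0.33 | 0.820 | 61% | 1.08 |
| 10% | 0.5 | 0.823 | 65% | 1.09 |
| 10% | 0.33 | 0.884 | 98% | 1.16 |

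At f = 5% the shift is ln(0.787/0.75)/0.0397 = 1.2 to ln(0.820/0.75)/0.0397 = 2.2 standard errors. A larger sample shrinks the standard error but not the shift.

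**4. How far this depends on the assumptions**

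For f = 10% and r = 0.5 (0.823 above), the HR falls to 0.790 if the HFNC arm carries half the NIV share, and to 0.760 if it carries an equal share. With r = 1.5 and f = 10%, all in NIV, it is 0.725, so the bias runs against HFNC.

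**5. Planned analyses that might cover it**

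The immortal-time analysis drops children assigned the day after admission. It keeps first-day starters, which is where children arriving on support would be expected. The comparison with G-computation and the single-cubicle negative control do not target the issue. No listed covariate identifies home NIV or the mode of support.

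**The case against.** Several points on the other side stand.

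- A reader might infer that home-NIV children fall almost wholly into the NIV arm. The article gives no distribution, so this is not shown. Arm-specific entry follows from the recording rule only for other-mode starters.
- A reader might infer that the plan calls the bias from exclusions 4 and 9 non-differential. It does not; that statement covers healthier children and pre-PICU starters. Home NIV could be read into the second case, where the assumption would be equally unsupported.
- A reader might take the remark about HFNC on the ward as an admission that pre-PICU initiation differs by arm. The remark concerns support after PICU discharge. The article neither supports nor refutes equal pre-PICU initiation.
- The direction requires slower liberation, and counting discharge as liberation caps the delay.
- Adjustment may absorb part of the effect. The candidate covariates include admission CPAP, mechanical ventilation, neurodegenerative disorder and previous PICU admission, and the list is open.
- Details of the analysis are left to a SAP that is not shown, so the absence of a targeted analysis can be stated only of this article. The article also admits that pre-PICU starters are not excluded.

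None of this rescues the contraindication argument for exclusions 4, 7 and 9.

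**Conclusion.** The stated justification is wrong for exclusions 4 and 9, and exclusion 7 does not fit it either. The resulting bias is probably differential. If the affected children are liberated more slowly, it favours HFNC and is anti-conservative for non-inferiority. Its size is unknown. The 23% to 61% at a 5% share, and 7% to 16% at a 2% share, are unadjusted illustrations that rest on an assumed relative hazard of 0.33 to 0.5 and on all such children being in NIV. They do not predict this study's error rate, and the documents do not support a claim that its conclusion will be biased by any given amount.

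Two smaller points follow. Non-differential pre-PICU initiation is a separate assumption for which the article gives no evidence. The new-user label needs qualifying, because exclusions 3 and 4 are both unapplied.

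**What to change.** **Wording**

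- Limit the contraindication argument to the criteria it fits: untreated air-leak and craniofacial anomalies.
- State that not applying exclusions 4 and 9 may load the NIV arm and probably favours HFNC.
- Present non-differential pre-PICU initiation as an untested assumption, and qualify the new-user label.

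**Pre-specified analyses**

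1. A sensitivity analysis restricted to admissions where support before PICU is unlikely, using fields already listed under Covariates ("source of admission, care area admitted from").
2. A quantitative bias (tipping-point) analysis over the share and relative hazard of home-NIV and other-mode children in the NIV arm, showing what contamination would overturn non-inferiority against 0.75. This is the only one of the three that addresses other-mode starters.
3. If daily records from earlier admissions are available, which the article does not show, exclusion of children whose previous stay ended on NIV. This is an imperfect proxy: it misses children with no earlier stay and flags some with acute NIV.

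Report these beside the primary result to support interpretation. Requiring non-inferiority in every subset is not warranted, because the subsets are smaller and differ in case mix.

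**Cost:** some wording, up to two subset reruns and one bias calculation, with less precision and a shifted case mix in the subsets.
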